##### Medication adherence

Medication adherence will be assessed with the Basel Assessment of Adherence to Immunosuppressive Medication Scale (BAASIS©) [43]. The BAASIS is divided into two parts. The first part consists of four questions, with the answer options ‘Yes’ (1) and ‘No’ (0). If ‘Yes’, to any of these items, the second part needs to be answered; the patient will be asked to answer how often they are non-adherent: ‘Never’ (1), ‘Once a month’ (2), ‘Every 2 weeks’ (3), ‘Every week’ (4), ‘More than once a week’ (5), ‘Every day’ (6). When one of the items of the first part is answered with ‘Yes’, the patient is considered non-adherent.

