### Data analysis

Data will be coded with a unique code per patient. The key of these codes will be safeguarded by the coordinating and the principal investigator with a password. No other persons will have access to the key. All data will be kept for 15 years, according to the Dutch Personal Data Protection law. Data will be stored using the data capture applications Gemstracker and Limesurvey. These systems are managed by the Department of Information Management of Erasmus MC and are secured with an individual password for the coordinating and principal investigator.

To assess if randomization has resulted in comparable groups, we will compare patients in the control and in the experimental period at baseline (T0) on characteristics as well as primary and secondary outcomes. Descriptive statistics will be presented as frequencies (%) for categorical variables. Continuous variables will be described as median and interquartile range for non-normally distributed variables and as mean and standard deviation for normally distributed data.

The primary analysis of the study is an initial univariate exploration of the effect of the intervention. Continuous outcomes at T1 between the patients in the control and experimental period will be compared and tested using the Mann-Whitney *U* test for non-normally distributed data and the independent-samples *t* test for normally distributed data. For the BAASIS, a 2 × 2 chi-squared test will be conducted (adherent yes/no × control/experimental group). In univariate analyses, the relationship between patient characteristics (such as age and gender) and medical characteristics (such as organ type and centre) and the outcomes will be assessed.

For the multivariate analyses, linear mixed models analysis will be conducted to account for repeated measures per patient, covariates organ and transplant centre and other significant covariates. All models will be estimated using intention-to-treat analysis incorporating all eligible patients from whom data was obtained. There are three measurement time points (T0, T1 and T2) to be included in these analyses. For missing data in predictor variables, we will use multiple imputation. A *p* value < 0.05 is considered statistically significant.

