We will assess the differences on the primary and secondary outcomes between patients in the control period and versus the experimental period at both T1 and T2 on the outcomes (between-groups comparison). We will also assess the differences on the outcomes between T0–T1 and T0–T2 within the control period and within the experimental period (within-groups comparison). The secondary outcome measure *medication adherence*, which is a dichotomous variable, will be analysed with a generalized estimating equations logistic regression. If the effect of the intervention is found to differ according to organ type then separate explorative multivariate analyses will be conducted to assess the effect per organ.

Among NPs, in an initial univariate analysis, we will compare self-management support skills, using all scales of the SEPSS-36, before and after the experimental period (T0-prior to training and T1-at the end of the implementation period). For non-normally distributed data, we will use the Wilcoxon signed-rank test and the paired samples *t* test in case of normally distributed data.

The video recordings of the NPs will be assessed in blocks of 5 minutes each. Of every recording, a 5-minute clip will be randomly assigned to be observed by two researchers independently. The clips from the control period will be compared with the clips of the experimental period on the needs-thwarting and needs-supporting subscales and tested using the Wilcoxon-signed rank test for non-normally distributed data and the paired samples t-test in case of normally distributed data.

The interviews and qualitative questions in the questionnaire, which will be used to qualitatively evaluate the intervention and the nurse-led care, will be transcribed by at least two researchers independently and analysed thematically [55] using NVivo.

To examine if contamination occurred, we will compare the primary outcome (Skills and Technique Acquisition - heiQ) among control period patients in the contamination phase versus those in the control period not in the contamination phase at T1 and T2. This will be done using an independent samples *t* test. If there is a significant difference, we will control for contamination in the main multivariate analysis.

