A second potential limitation is that the effect on the patients is dependent on the effectiveness of the training in bringing change among the NPs. The fact that NP’s spend extra time with the patient could also increase patients’ self-management skills. To identify if an increase of patients’ self-management skills is affected by the intervention, we will conduct an evaluation of the intervention fidelity and ask patients to evaluate the programme.

Another potential limitation is response burden due to the amount of questionnaires patients’ need to complete. At each point in time, the patients are required to complete four questionnaires, which together comprise 117 questions and time to complete the questionnaires will be approximately 30 min. It has been suggested that shorter questionnaires can increase response rate and that respondents will be less likely to drop out and to complete the questionnaire if it takes 10 min compared to when it takes 30 min to complete [57]. Although there is a chance of response burden, we decided to accept this due to the fact that these questionnaires are the most appropriate to answer the research questions.

Another strength of the study is that we have broadened the target group to include other organ types, compared to the pilot study [22]. In the initial pilot study, the target group consisted of kidney transplant recipients, but we believe and research has shown, that self-management support is important for all transplant recipients regardless of the organ [13, 19, 20]. While the cause of organ failure differs, the post-transplant treatment regime, accompanying challenges and needs such as adjusting daily life, food hygiene and immunosuppression, but also psychosocial challenges are partly the same. Therefore, this study will include patients who received a heart, kidney liver or lung transplantation and still have a homogeneous study group. If found to be effective, we will have evidence to support implementation among all these transplant recipients.

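### Imputation is named for predictors only, so dropout linked to earlier non-adherence can bias the available-case BAASIS analyses, chiefly the within-period changes

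*Protocol article*

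**What the plan says.** The protocol article makes BAASIS a yes/no outcome: "When one of the items of the first part is answered with ‘Yes’, the patient is considered non-adherent" (Medication adherence). It is collected at T0, T1 and T2 in both periods.

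The Data analysis section plans two analyses of it. The first is a 2 × 2 chi-squared test of adherence by period. Read with the sentence before it, this is at T1, and it belongs to the univariate step that the article calls its primary analysis. The second is for the repeated measures: adherence "will be analysed with a generalized estimating equations logistic regression". No working correlation or weighting is given. The comparisons wanted are control against experimental period at T1 and T2, and also the "differences on the outcomes between T0–T1 and T0–T2 within the control period and within the experimental period".

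On incomplete data the same section says "All models will be estimated using intention-to-treat analysis incorporating all eligible patients from whom data was obtained" and "There are three measurement time points (T0, T1 and T2) to be included in these analyses". The one imputation rule is "For missing data in predictor variables, we will use multiple imputation". Under Strengths and limitations, the article discusses dropout from a 117-question, 30-minute survey and concludes "Although there is a chance of response burden, we decided to accept this".

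**The concern.** The continuous outcomes go into a linear mixed model. That model is likelihood-based and, if correctly specified, remains valid when missingness depends on observed earlier answers. Unweighted GEE has no such general protection. It needs missingness that is completely random or explained by the covariates in the model, unless the working correlation is close to the truth. The chi-squared test uses only patients observed at T1 and ignores their T0 answers. So the same missing-data rule serves the continuous outcomes reasonably well and leaves the binary one exposed.

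Adherence is named in the first study aim. If patients who were non-adherent at one visit are less likely to return the next questionnaire, those who remain look more adherent. A fall in non-adherence within a period could then be partly or wholly dropout. If this selection works differently in the two periods, the comparison between periods is distorted too.

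**Working it through.** The article gives no adherence rate, dropout rate or working correlation, and no figure for adherence that could be reproduced. Its only guide to dropout is the step from 82 to 100 patients per group, at most 18%, which also has to cover covariate adjustment and contamination. The inputs below are therefore assumptions.

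**Inputs.** True non-adherence is 35% at every visit in both periods, so all true ORs are 1. Adherence at successive visits follows a latent normal variable with correlation 0.6. T1 dropout depends on T0 status.

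**Step 1: persistence.** Under these assumptions the probability of being non-adherent at both T0 and T1 is 0.2138. Hence:
- P(non-adherent at T1 | non-adherent at T0) = 0.2138/0.35 = 0.611
- P(non-adherent at T1 | adherent at T0) = (0.35 − 0.2138)/0.65 = 0.210

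**Step 2: within-period change, same dropout in both periods (10% if adherent at T0, 30% if not).**
- Retained: 0.65 × 0.90 + 0.35 × 0.70 = 0.585 + 0.245 = 0.830 (17% lost)
- Observed non-adherence at T1: (0.245 × 0.611 + 0.585 × 0.210)/0.830 = 0.328, against a true 0.350
- Change OR: (0.328/0.672)/(0.35/0.65) = 0.488/0.538 = about 0.91, true value 1

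A simulation with all three visits, analysed by GEE with working independence, gave change ORs of about 0.81 to 0.90; the T1 result above lies at its upper end. Because both periods show the same false fall, the OR between them stays at 1.

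**Step 3: between-period OR, dropout differing by period (control 10%/40%, experimental 15% regardless).**
- Control retained: 0.585 + 0.35 × 0.60 = 0.795 (20.5% lost)
- Control observed non-adherence: (0.210 × 0.611 + 0.585 × 0.210)/0.795 = 0.316. In the first product, 0.210 is the retained share 0.35 × 0.60; in the second it is the probability from Step 1.
- Experimental observed non-adherence: 0.350, unbiased
- OR, experimental against control: 0.538/0.461 = 1.17, true value 1

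Simulation gave 1.16 to 1.19. With the two dropout rules swapped the OR is 0.86. With latent correlation from 0.4 to 0.8, the 1.17 runs from 1.10 to 1.26. A period-by-time GEE with working independence reproduces the observed proportions, so the T1 figure applies equally to the chi-squared comparison.

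**Step 4: other inputs and the working correlation.** Here non-adherence was set at 35/38/42% in the control period and 35/28/30% in the experimental period, with latent correlation 0.6 and dropout at each interval of 5% if adherent and 25% if not, in both periods.

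| Quantity | Full data | GEE, independence | GEE, exchangeable | Imputation-type estimate |
|---|---|---|---|---|
| Between-period OR, T2 | 0.576 | 0.582 | 0.582 | 0.578 |
| Control change OR, T0–T2 | 1.336 | 1.114 | 1.318 | 1.337 |
| Experimental change OR, T0–T2 | 0.798 | 0.672 | – | 0.801 |

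The within-period ORs move by about 16 to 17%, and the between-period OR by about 1%. When the dropout rule differed by period, the T2 OR under independence moved from 0.588 to 0.694 (control 5/25, experimental 12/12) and from 0.598 to 0.438 (control 10/10, experimental 5/35). Exchangeable GEE gave 0.588 and 0.583 in those two cases. When the true correlation decayed over time, exchangeable GEE kept a bias of roughly 2 to 5%. With completely random dropout there was no material bias.

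**The case against.** - **The size depends on working independence, which the article does not specify.** This is right and shrinks the point. In the Step 3 scenario, exchangeable GEE gave 1.011 where independence gave 1.169 (true value in that run 1.004). It does not remove the point, because the chi-squared test at T1 uses no earlier measurement and no working correlation can help it.
- **A reader might infer that dropout linked to earlier non-adherence biases the between-period OR in any case.** It does not: under a common rule that OR is essentially unbiased. Both periods get the same questionnaires and two reminders, and the researcher rather than the nurse practitioner sends the questionnaires, which argues against different rules. The trial is unblinded and the intervention adds nurse contact, so a difference is plausible, but nothing in the article shows one. Nor does it show that patients who miss medication miss surveys.
- **Outcome imputation is detail for an analysis plan that is not shown.** The choice of working correlation is such detail. But the article does state a missing-data rule, restricts it to predictors, and names the adherence methods. A reader might go further and infer a decision never to impute outcomes; the article does not say so. Leaving outcomes unimputed is the natural reading, not a quotation.
- **The bias is small against the precision.** With 35% non-adherence and about 85 observed per group, the standard error of the log OR is √(2/(85 × 0.35 × 0.65)) = 0.32, a 95% interval of about 0.53 to 1.88 around 1. ln 1.16 = 0.15 is just under half a standard error. That is fair, and it limits the weight of the point. The bias would not shrink with more patients, however, and it is cheap to reduce.

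**Conclusion.** The point holds in limited form. As written, BAASIS would be analysed from available answers by two methods that do not in general tolerate dropout depending on earlier adherence.

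The within-period changes are the most exposed, because they can be biased even with the same dropout pattern in both periods: about 0.81 to 0.90 for a true 1 under the assumed 35% non-adherence, 10%/30% dropout and working independence. Material bias between periods needs a link between dropout and adherence that differs by period, as in the 1.16 to 1.19 example. A well-chosen working correlation removes most of this from the GEE and none of it from the chi-squared test.

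All rates are assumptions, and the direction of any bias in the actual trial is unknown. Adherence is a secondary outcome, and the primary heiQ result is not affected.

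**What to change.** Extend the multiple imputation already planned to missing BAASIS outcomes at T1 and T2. The imputation model should contain period, department, organ, earlier BAASIS, T0 heiQ and the covariates. Run both the GEE and the T1 between-period comparison on the imputed data sets and pool the results. State a non-independence working correlation for the GEE. Keep the available-case chi-squared test and GEE as sensitivity analyses.

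The cost is a sentence or two in the plan and a little more analysis work; no new data are needed. The downside is reliance on a missing-at-random imputation model, which would not correct dropout that depends on the unobserved current adherence itself. The change is best made before outcome data are examined.

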## Methods/design

### Study design and randomization

This multi-centre study in the Netherlands has an unblinded stepped wedge cluster randomized design [32] with pre- (T0) and post-intervention measures after six months (T1), with a follow up after twelve months (T2). The framework of this trial is superiority, whereby we will compare the outcomes between the control and intervention group, and between baseline and follow up data. Seven departments of five University Medical Centres will participate in the study, four kidney transplantation units, one heart transplantation unit, one liver transplantation unit and one lung transplantation unit. The coordinating centre is Erasmus MC, department Nephrology and Transplantation. This department is responsible for coordinating the study, distributing the questionnaires, training of the NPs and the data analysis. A steering committee is present to contribute ideas and to oversee the process.

Given the nature of the programme and the fact that NPs are trained in delivery of the intervention and communication skills, the NPs delivering the intervention cannot be blinded to the group allocation. Therefore, randomization will be performed at the department level. This will be carried out by an independent professional not involved in the study using sealed opaque envelopes. The envelopes with department names and envelopes with start date will be prepared and shuffled by the researcher. The independent professional then randomly chooses the envelopes. All seven participating departments commence the study with standard care i.e. the control period (see Fig. 1) in September 2020. The timing of transition of departments from control to experimental  period is randomized. The first department will be randomized to commence the experimental period in March 2021. During the experimental period, patients receive standard care plus the ZENN intervention. Patients in the control period are different from the experimental period patients, meaning that they will not cross-over.

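### The planned exploratory models per organ have no concurrent control department for heart, liver and lung, so in those three organs they reduce to a small before-after comparison

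*Protocol article*

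**What the plan says.** All references are to the protocol article.

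- **Study design and randomization.** The participating departments are "four kidney transplantation units, one heart transplantation unit, one liver transplantation unit and one lung transplantation unit", and "randomization will be performed at the department level". What is randomised is when each department switches: "The timing of transition of departments from control to experimental" period. There is a common start: "All seven participating departments commence the study with standard care i.e. the control period". The two periods hold successive cohorts: "Patients in the control period are different from the experimental period patients, meaning that they will not cross-over".
- **Data analysis.** The main model is a linear mixed model with repeated measures per patient, organ, transplant centre and other significant covariates. On organs, the text is conditional. Only where the effect turns out to vary between organs does this follow: "separate explorative multivariate analyses will be conducted to assess the effect per organ".
- **Sample size.** The calculation covers the overall T1 comparison only: effect size 0.38, 82 per group, raised to 100 per group (200 in total). No number per organ and no baseline correlation is given.
- **Strengths and limitations.** The argument for including four organs ends: "If found to be effective, we will have evidence to support implementation among all these transplant recipients". The section does not mention that three organs have one department each.

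**The concern.** A stepped wedge separates the intervention from calendar time by comparing, at the same date, departments that have switched with departments that have not. That comparison needs at least two departments with different switch dates. A heart-only, liver-only or lung-only model has one. Every control patient in it enrols before every experimental patient, and random assignment of the switch date supplies no contrast within it.

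A change over time in self-management scores would then be indistinguishable from an intervention effect. Such change is plausible: the article itself notes that the COVID-19 pandemic may move the intervention and the training to remote delivery. The condition adds a second difficulty. If organ estimates are produced only after a difference has been detected, and the test for it has little power, the contrasts that reach the reader will tend to be exaggerated.

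**Working it through.** **1. The plan's own figure.** For two means, n per group = 2 × ((1.960 + 0.842) / 0.38)² = 108.7, or 109 without baseline adjustment. ANCOVA multiplies this by (1 − ρ²), where ρ is the correlation between T0 and T1. With ρ = 0.5, 108.7 × 0.75 = 81.5, so 82, which matches Sample size. The article does not state ρ; 0.5 is the value that reproduces its figure.

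**2. Can the effect be separated from calendar period?** I set up a design matrix with department effects, free period effects and a treatment indicator. Eight periods and a different switch time for each department are assumed, because the flowchart is not legible here.

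| Model | Columns | Rank | Treatment estimable |
|---|---|---|---|
| All seven departments, one effect | 15 | 15 | yes |
| Four kidney departments only | 12 | 12 | yes |
| One department only | 9 | 8 | no |
| All seven, one effect per organ, shared periods | 18 | 18 | yes, all four |

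For one department the rank is also 8 without the treatment column, so treatment is fully aliased with period. The last row keeps full rank for every order of the seven switch times. If a single department were given a linear trend instead of free periods, the effect would be estimable by assumption. Its variance would be inflated by 1.5 (switch after the first or before the last period) to 4.2 (switch midway).

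**3. Size of a single-organ comparison.** Assume an equal split: 200 / 7 = 28.6 per department, and 28.6 / 2 = 14.3 per period. Power is for a two-sided t test at 0.05, with noncentrality (0.38 / √(1 − ρ²)) × √(n/2) and no time term.

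| ρ | Noncentrality at n = 14.3 | Power | Effect detectable at 80% |
|---|---|---|---|
| 0 | 0.38 × 2.673 = 1.02 | 17% | 1.09 SD |
| 0.5 | 0.439 × 2.673 = 1.17 | 20% | 0.94 SD |
| 0.7 | 0.532 × 2.673 = 1.42 | 28% | 0.78 SD |

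Because the split is unknown, I also took 5 to 25 patients per period. Power then runs from 8% (5 patients, ρ = 0) to 45% (25 patients, ρ = 0.7).

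**4. Drift, as an illustration.** Trial status gives inclusion from September 2020 to May 2022, about 21 months. With uniform enrolment and a switch at month s, the mean enrolment times are s/2 and (s + 21)/2. They differ by 10.5 months whatever s is. The documents give no drift rate; assume 0.2 SD per year.

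- Unadjusted T1 comparison: 0.2 × 10.5/12 = 0.175, about 0.18 SD.
- Adjusted for T0 with slope 0.5, if T0 and T1 drift equally: 0.175 × (1 − 0.5) = 0.0875, about 0.09 SD.
- Change from T0 under the same equal drift: it cancels. Only drift that affects T1 beyond T0 enters in full.

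**The case against.** The strongest reply is that the plan already limits these analyses. They are run only if the effect differs by organ, they are labelled explorative, and the trial is powered on the overall comparison alone. That stands, and it keeps the point away from the primary result. Low power in an exploratory subgroup is also ordinary and is not in itself an error. But the label does not create a concurrent control, and the choice of separate models is stated in the article rather than left to a fuller document.

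Three stronger readings are tempting and not supported.

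- A reader might infer that organ results will be presented as confirmed trial effects, or that a non-significant one will be read as no effect. Nothing in the text says so.
- A reader might take the closing sentence on implementation as a claim of a proven effect in each organ. It generalises from the pooled result, on the argument that post-transplant regimes and challenges are partly the same, and does not rest on the per-organ models.
- A reader might carry the 0.18 SD drift into the planned models. It holds for an unadjusted T1 comparison; with T0 in the model it can be half that or less.

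It is also fair to say that the pooled interaction model moves the assumption rather than removing it. It relies on period effects common to all organs, and for heart, liver and lung the organ remains the same thing as the department.

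**Conclusion.** The point holds for the three single-department organs. Their separate models would be uncontrolled before-after comparisons, with treatment fully aliased with period unless a shape for the time trend is assumed. It does not hold for kidney, provided its four departments switch at different times, and it says nothing against the overall comparison.

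The aliasing follows from the stated design. The power of about 17% to 28% rests on an equal split and on baseline correlations of 0 to 0.7; the wider range is 8% to 45%. The drift figures of 0.18 and 0.09 SD illustrate an assumed rate and are not estimates. Since the analyses are contingent and exploratory, this is a worthwhile correction to a secondary part of the plan, not a threat to the trial's main conclusion.

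**What to change.** In Data analysis, replace the separate models per organ by an intervention-by-organ interaction in the pooled mixed model, with department effects and period effects shared across departments. Report the four organ estimates with confidence intervals, marked exploratory, whatever the interaction p-value.

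State two limits next to them. First, common period effects across organs are assumed. Second, heart, liver and lung each rest on one department, so an organ difference cannot be told apart from a department or nurse-practitioner difference. In Strengths and limitations, say that the evidence is for the average effect over the seven departments.

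The cost is wording, the interaction terms and the shared period terms, which the article does not name for its mixed model. No new data are needed. The downside is the common-period assumption: if time trends differ between organs, the heart, liver and lung estimates absorb that difference.

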## Trial status

Start of inclusion; September 2020, expected end of inclusion May 2022.

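### The separate per-organ models for heart, liver and lung are single-department before-after comparisons, so an organ-specific effect cannot be separated from calendar change at that site

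*Protocol article*

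**What the plan says.** Study design and randomization lists the clusters as "four kidney transplantation units, one heart transplantation unit, one liver transplantation unit and one lung transplantation unit". It states that "randomization will be performed at the department level" and that "All seven participating departments commence the study with standard care i.e. the control period". What is left to chance is the switch date: "The timing of transition of departments from control to experimental" period. The two periods hold different people: "Patients in the control period are different from the experimental period patients, meaning that they will not cross-over". On dates, "The first department will be randomized to commence the experimental period in March 2021", and Trial status gives "Start of inclusion; September 2020, expected end of inclusion May 2022".

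Under Data analysis, if the intervention effect turns out to depend on organ type, "separate explorative multivariate analyses will be conducted to assess the effect per organ". The multivariate model described there is a linear mixed model with repeated measures (T0, T1, T2), organ, transplant centre and other significant covariates. T0 to T2 are times since a patient's own baseline. No calendar-time or step term is named. Strengths and limitations does not mention that three organs are represented by one department each.

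**The concern.** In this design the randomised information lies in comparing departments that have switched with departments that, at the same calendar time, have not. A model restricted to heart, liver or lung patients holds one department. All its control patients are enrolled before all its ZENN patients, and nothing in that model shows what would have happened at the same time without ZENN.

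This is not a detail that can be left to a later analysis plan. The article fixes the method as separate models, and adding period terms to a one-department model cannot repair it. At stake is an organ-specific estimate that looks like a trial result but is an uncontrolled before-after difference, over a time when the article itself expects pandemic-related changes in how care and training are delivered.

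**Working it through.** **Inputs from the article.** Departments: kidney 4, heart 1, liver 1, lung 1. First switch March 2021 (month 6). Inclusion September 2020 to May 2022, so 20–21 months. Planned effect 0.38 SD, 82 patients per group for 80% power at two-sided 0.05, 100 per group recruited.

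**Assumptions (not in the article).** Later switch dates, even inclusion, size of any calendar trend, and baseline-outcome correlation ρ.

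**1. The article's own figure.** n per group = 2(1 − ρ²)(1.960 + 0.842)² / 0.38². With ρ = 0.5 this is 2 × 0.75 × 7.849 / 0.1444 = 81.5, so 82, as stated. With ρ = 0 it is 109, and with ρ = 0.6 it is 70. A residual variance of 0.75 therefore agrees with the plan. The figure concerns the pooled trial; none is given per organ.

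**2. Estimability with categorical period effects.** Design matrix: department effects, 8 assumed periods with boundaries at the switch dates, and the intervention indicator.

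| Departments in model | Columns | Rank | Intervention effect |
|---|---|---|---|
| All seven | 7 + 7 + 1 = 15 | 15 | estimable |
| Four kidney (any four distinct start dates) | 4 + 7 + 1 = 12 | 12 | estimable |
| One (any start date) | 1 + 7 + 1 = 9 | 8 | not estimable |

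In one department the intervention indicator equals the sum of the indicators for the periods after the switch.

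**3. Linear time instead.** The effect becomes estimable, but only as a departure from an assumed straight line. For a switch at month 12 of 21 the variance inflation is 3.8. In simulation (28 patients) the SE roughly doubles, from 0.34 to 0.69 SD.

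**4. Size of the confounding.** With even inclusion over T months and a switch at month s, mean enrolment is s/2 for control and (s + T)/2 for ZENN patients. The gap is T/2 for every s: 10 months for T = 20, 10.5 for T = 21. False effect = yearly trend × 10.5/12. If the trend moves T0 and T1 equally and baseline is adjusted for with slope 0.5, it is multiplied by 1 − 0.5.

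| Trend (SD per year) | Trend on T1 only | Share of 0.38 | T0 and T1 equally, slope 0.5 |
|---|---|---|---|
| 0.05 | 0.04 | 12% | 0.02 |
| 0.1 | 0.09 | 23% | 0.04 |
| 0.2 | 0.18 | 46% | 0.09 |
| 0.3 | 0.26 | 69% | 0.13 |

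**5. Precision.** Assumed layout: switches every 2 months from month 6 to 18, inclusion to month 20, 100 control and 100 ZENN patients, accrual even within each condition, residual variance 0.75. Control time totals 6 + 8 + … + 18 = 84 department-months and ZENN time 14 + 12 + … + 2 = 56. Separate-model SE = √[0.75(1/n_c + 1/n_z)]. For the month-6 switch, n_c = 6 × 100/84 = 7.1 and n_z = 14 × 100/56 = 25, so SE = √(0.75 × 0.18) = 0.37. The pooled SE is from weighted least squares with department effects, shared 2-month period effects and organ-by-intervention terms.

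| Switch month | 6 | 8 | 10 | 12 | 14 | 16 | 18 |
|---|---|---|---|---|---|---|---|
| Separate model, no period terms | 0.37 | 0.34 | 0.32 | 0.32 | 0.34 | 0.38 | 0.49 |
| Pooled model, shared periods | 0.42 | 0.39 | 0.38 | 0.38 | 0.39 | 0.43 | 0.55 |

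Dividing the rounded entries gives increases of about 12–19%; before rounding they are 11–16%. The 95% half-widths are 0.6–1.0 SD (separate) and 0.74–1.08 SD (pooled).

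**6. The pooled model as written.** With a trend of 0.2 SD per year and no true effect, simulating seven departments without a time term gives a mean estimate of 0.17 SD, against 0.18 SD by the formula for one department. Adding a time term brings the seven-department estimate to about 0.

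**The case against.** The strongest reply is that these analyses are labelled exploratory and run only if an organ difference is found. That stands as a limit on the consequence. The label warns of low power and multiplicity, however, not of the loss of any concurrent comparator.

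A reader might infer that any calendar trend passes in full into the organ estimate. The article does not support that. T0 is in the mixed model and within-group changes from T0 are planned. A trend that moves T0 and T1 equally is about halved by baseline adjustment with slope 0.5 and cancels in a change-score contrast. A trend that affects T1 but not T0, such as altered clinic contact during follow-up, is not removed.

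A reader might also infer that splitting by organ is what introduces the bias. As the article stands it is not: the pooled model names no calendar term either and is biased by nearly the same amount (step 6). The difference is that the pooled model can be repaired by adding a term and the one-department models cannot. The gain from pooling therefore depends on period terms being in the pooled model.

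It is also fair to say that shared period effects remove only trends common to the departments. Staff or case-mix changes at the one heart, liver or lung site stay confounded under either approach, and both give intervals too wide for firm organ-specific conclusions. Finally, testing whether the effect differs by organ already implies a comparison on pooled data; the fix keeps that model for estimation.

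**Conclusion.** The point holds in limited form. On the article's own design, a separate heart, liver or lung model is a single-site before-after contrast whose intervention effect cannot be separated from calendar change at that site. Categorical period terms are fully aliased with the intervention, and a linear term rests on the straight-line assumption. Kidney, with four departments, is not affected once period is modelled.

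The possible false effect is about 0.04–0.26 SD for trends of 0.05–0.3 SD per year acting on T1 only, and about 0.02–0.13 SD if the trend is shared by T0 and T1 and baseline is adjusted for with slope 0.5. These figures rest on even inclusion over 20–21 months and on assumed trends; the article gives no trend, and none has been shown to exist. The aliasing does not depend on those assumptions. Because the analyses are exploratory and conditional, the primary comparison is untouched by this point. It should be corrected because the change is cheap.

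**What to change.** Replace the per-organ sentence in Data analysis with:

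> *Exploratory effects per organ are estimated from the mixed model on all seven departments, with organ-by-intervention terms and calendar-period effects shared across departments; no separate models are fitted for heart, liver or lung. Each of these estimates comes from one department, so organ cannot be separated from department, and changes specific to that department remain confounded with the intervention.*

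Kidney may also be fitted alone with period terms. The change needs period terms in the pooled model; without them it gains almost nothing.

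Cost: one sentence and no new data. The organ SEs rise to 0.38–0.55 SD under the assumed layout, so the estimates stay imprecise, and the calendar trend has to be assumed common to the organs. That assumption is weaker than the absence of any trend, which the separate models rely on.
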